## List of used abbreviations

|       |                                    |
|-------|------------------------------------|
| MPA   | Medical Products Agency            |
| SmPC  | Summary of Product Characteristics |
| CRF   | Case Record forms                  |
| SAR   | Serious adverse event              |
| SUSAR | Suspected unexpected adverse event |
| CSP   | Clinical Study Protocol            |

## Synopsis

*Mycoplasma pneumoniae* is one of the leading causes of community acquired pneumonia. Although normally self-limiting, a proportion of patients develop more severe infection and have to be admitted to hospital. Available data suggests that corticosteroids are beneficial for severe *M. pneumoniae* pneumonia in children and for all-cause community acquired pneumonia. However, the corticosteroid doses tested are high and data on adults admitted to hospital with *M. pneumoniae* pneumonia is lacking. The aim of this randomised, controlled, multicentre trial is to determine if oral intake of 12 mg (total dose) of betamethasone over 5 days, as an adjunct to antibiotics, is beneficial for the treatment of adults hospitalised with *M. pneumoniae* pneumonia. The primary endpoint of this study is time to resolution of hypoxemia. Secondary endpoints include time to discharge from hospital, improvement in subjective well-being, shortness of breath and cough as determined by a standardised questionnaire, time to resolution of fever, impact on eradication of *M. pneumoniae* and identifying inflammatory fingerprints for prediction of severe *M. pneumoniae* infection. We assume resolution of hypoxemia by 48 hours in 95% of participants with betamethasone and 65% of those without betamethasone. In order to detect this with 90% power, 70 adult patients hospitalised with *M. pneumoniae* pneumonia at any of our study hospitals during the course of two years will be included. EudraCT number 2016-002585-32.

## Background

*Mycoplasma pneumoniae* is one of the leading causes of community acquired pneumonia. Respiratory symptoms are typically dominated by cough. *M. pneumoniae* pneumonia is normally self-limiting, however cough and fatigue may last for many months and be quite debilitating (1). A proportion of patients develop more severe infection and have to be admitted to hospital. Characteristics of these patients are younger age, fewer comorbidities and lower mortality compared to other causes of community acquired pneumonia (2). Despite being young and with no comorbidities these patients tend to have high breathing rates and considerable oxygen demand resulting in hospitalisation.

The severity of *M. pneumoniae* pneumonia appears to be dependent upon the immune response through various mechanisms including an allergic reaction as well as the bacterial load (2). In line with this, corticosteroids have been reported to be beneficial in children with refractory *M. pneumoniae* pneumonia. Three case series using high doses of corticosteroids reported rapid improvement (3-5). A randomised trial (n=58) in which the treatment group received 1 mg/kg oral prednisolone twice daily for 5 days in addition to azithromycin found that the duration of fever, hypoxemia and dyspnoea were shorter in the treatment group. Resorption of pulmonary infiltrates and atelectasis were also faster (6). These patients had refractory *M. pneumoniae* pneumonia defined as prolonged fever and deterioration of clinical and radiological findings after 7 days of azithromycin treatment. Another study randomised children admitted for *M. pneumoniae* pneumonia to prednisolone treatment within 24 or 72 hours and found that fever duration, hospital stay and radiographic resolution were faster with earlier treatment (7).

A recent study found 50 mg of prednisolone daily for 7 days to be beneficial for treatment of adults with all-cause community acquired pneumonia (8). Asthma is typically treated with 30-60 mg prednisolone or 4-8 mg betamethasone daily until improvement or for 10 days (9). However, studies on corticosteroid use in adults hospitalised with *M. pneumoniae* pneumonia are lacking.

## Aim

The aim is to determine if corticosteroid treatment, as an adjunct to antibiotics, is beneficial for the treatment of adults hospitalised with *M. pneumoniae* pneumonia.

## Rationale

Data and clinical impression suggests that much of the illness associated with *M. pneumoniae* pneumonia is driven by inflammation and consequently corticosteroid treatment should be beneficial. Available data suggests that corticosteroids are beneficial for severe *M. pneumoniae* pneumonia in children and for all cause community acquired pneumonia in adults. However, the corticosteroid doses used are high and data on adults admitted to hospital with *M. pneumoniae* pneumonia is lacking. Based on studies in children the potential benefits are faster symptom resolution and shorter hospital admittance.

## Benefit-risk assessment

In this study we will use betamethasone (ATC H02AB01) given orally according to the Summary of Product Characteristics (SmPC) in a dose that is expected to be well tolerated. Possible adverse events of this treatment include hyperglycemia, hypertension, gastric ulcers and mood changes amongst others. Blood samples taken in the study may be painful, but are not harmful. Possible benefits include shorter time to recovery and the extended follow-up will enable a more rapid detection of possible treatment failures. Additionally, the risk of developing severe mycoplasma pneumonia requiring intensive care treatment is likely to be reduced in future patients should betamethasone treatment prove to be effective. We therefore deem the potential benefits of this study superior to the potential risks.

## Outcomes

Primary endpoint: Time to resolution of hypoxemia defined as no longer requiring supplemental oxygen to maintain a peripheral oxygen saturation above 92% measured with pulse oximetry after 20 minutes rest and a breathing rate of  $\leq 20$  breaths per minute.

Secondary endpoints: Secondary endpoints include time to discharge from hospital, improvement in subjective well-being, shortness of breath, and cough as determined by CAP score questionnaire, time to resolution of fever, impact on eradication of *M. pneumoniae* and identifying inflammatory fingerprints for prediction of severe *M. pneumoniae* infection.

## Methods

### Study Design

An open, randomised, controlled, multicentre, clinical trial conducted at the following hospitals in Sweden: Akademiska sjukhuset (Uppsala), Capio S:t Görans sjukhus (Stockholm), Danderyds sjukhus (Stockholm), Hallands sjukhus Halmstad, Helsingborgs lasarett, Mälarsjukhuset (Eskilstuna), Norrlands Universitetssjukhus (Umeå), Sjukhuset i Gävle, Skaraborgs sjukhus Skövde, Skånes Universitetssjukhus Lund, Skånes Universitetssjukhus Malmö, Södersjukhuset (Stockholm), Universitetssjukhuset i Linköping and Östersunds sjukhus. The study will be conducted in accordance with the Helsinki declaration on ethical principles for medical research involving human subjects.

### Study population

Patients with *M. pneumoniae* pneumonia admitted to a study hospital will be considered for study entry. Patients will be identified by notification from the respective hospitals Microbiological Laboratory and by referral from colleagues. Patients will be informed of the study and offered to participate if they match inclusion and exclusion criteria. Upon inclusion case record form A will be filled in (appendix 1) and the informed consent form will be signed.

Inclusion criteria: Age  $\geq 18$  years, active *M. pneumoniae* pneumonia defined as chest x-ray or CT-scan showing an infiltrate and positive *M. pneumoniae* PCR on sample taken from upper or lower airways, admitted to a study hospital, hypoxemia defined as having a peripheral oxygen saturation below 93% (measured by pulse oximetry) and a breathing rate of  $>20$  breaths per minute without supplemental oxygen treatment, a negative pregnancy test taken before inclusion and usage of an acceptable effective method of contraception until treatment discontinuation if the participant is a woman of childbearing potential, written informed consent after meeting with a study physician and ability and willingness to complete follow up.

Exclusion criteria: Significant growth of alternative lower airway pathogen such as *Streptococcus pneumoniae* or *Haemophilus influenzae* in sputum, known current gastric ulcer, pregnancy, breast feeding, diabetes mellitus, chronic obstructive airway disease, asthma, hypersensitivity to any ingredient in the bethamethasone, inability to give informed consent or significantly compromised immunity. Compromised immunity includes but is not limited to

treatment with major immunosuppressive agents including high dose corticosteroids, anti-TNF agents, calcineurin inhibitors, mTOR inhibitors, lymphocyte depleting biological agents, chemotherapeutic anti neoplastic agents. Also patients with advanced HIV/AIDS, severe immunodeficiency such as hypoglobulinemia, decompensated liver cirrhosis and bone marrow transplant the last year will be excluded.

Patient screening and patient identification logs: Investigators will keep a record of all patients that are considered for enrolment even if they are not subsequently enrolled in order to verify that the patient population was selected without bias (ICH-GCP 8.3.20). The reasons for non-eligibility are to be defined in terms of one or more of the eligibility criteria.

### **Study Procedures**

Randomisation: All participants will be randomised to either a treatment group or a control group (A or B) using [www.sealedenvelope.com](http://www.sealedenvelope.com). Randomisation is blocked (using random permuted blocks) with 1:1 allocation ratio to ensure that the groups are balanced periodically.

Treatment: All participants will take doxycycline (ATC J01AA02) 200 mg once daily until 10 days total effective treatment has been taken. If participants have been treated with active antibiotics before inclusion, treatment will be switched to doxycycline upon inclusion. Total effective antibiotic treatment duration will be 10 days. The doxycycline dose chosen is slightly higher than normal as the doxycycline minimal inhibitory concentration is very similar to that obtained when 100 mg is given daily. The treatment duration is ten days as this group of patients have complicated mycoplasma pneumonia.

Participants randomised to treatment with betamethasone will take 3 mg once daily days 1 and 2 and 2 mg once daily days 3, 4 and 5, given orally according to the SmPC.

Betamethasone intake will be observed whilst admitted and confirmed by questioning thereafter. After discharge, any remaining doses will be labelled with dose information as done in standard clinical practice and given to the patient to take at home.

The betamethasone dose has been selected based on clinical experience, similarity to that used for treatment of exacerbations of chronic obstructive pulmonary diseases and asthma, tolerability and likely acceptance by clinical practitioners.

Betamethasone (ATC H02AB01) is a corticosteroid with a Marketing Authorization in Sweden (MA number 6940). It will be provided free of charge to participants and taken from

the pharmaceutical store room of the ward. As the drug only is administered directly from the ward, no study specific marking - except dose to be taken - is needed.

Patients randomised to the control group will only receive standard care with doxycycline as described above.

Monitoring and follow up: Whilst admitted breathing rate, peripheral oxygen saturation (measured with pulse oximetry after 20 minutes of rest), oxygen use, pulse, blood pressure, body temperature, peak expiratory flow and mental state will be monitored three times daily and entered into computerised medical records.

Medical records will be searched to determine values prior to inclusion in the study and data will be entered on to clinical records form B (appendix 2). Chest x-rays or CT scan will have been performed routinely prior to inclusion.

Following inclusion, participants will also be followed up with structured questionnaires (appendix 3, 4 and 5) to identify the community acquired pneumonia (CAP) score on days 1, 2, 3, 4, 5, 6, 7, 14, 28, 42 and at 2 months after inclusion. If the patient has been discharged, physiological parameters will not be recorded but the CAP score will be obtained per telephone. The CAP score is a disease-specific activity score for community acquired pneumonia; it ranges from 0 to 100, 0 marking the worst and 100 the best score (10).

Blood samples for analysis of C-reactive protein (CRP), white blood cell count (WBC) and haemoglobin (Hb) will be taken daily until normalised or discharge from hospital and on day 28. Fasting blood glucose and blood samples for immunological analyses will be taken daily until discharge and on day 28. Blood samples for *M. pneumoniae* serology will be taken on the day of inclusion and at day 28. A sample for diagnostic PCR and for subsequent phenotypic and genotypic characterisation of *M. pneumoniae* bacteria will be taken from upper airways prior to inclusion, upon inclusion and on day 28. Samples will be frozen at -80°C until phenotypic and genotypic characterisation. Patients will be discharged from the hospital at the discretion of treating physician. Follow up visits will be done on day 28 and by phone on days 42 and 56.

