**Table 1. Planned questionnaire and sampling follow up**

| Time point (days)                           | Prior to or upon
inclusion | Daily whilst
admitted | 7 | 14 | 28 | 42 | 56 |
|---------------------------------------------|-------------------------------|--------------------------|---|----|----|----|----|
| Clinical records form A                     | X                             |                          |   |    |    |    |    |
| Clinical records form B/C                   |                               | X            | X | X  | X  | X  | X  |
| Sampling                             |                               |                          |   |    |    |    |    |
| CRP, WBC, Hb                                | X                             | X            |   |    | X  |    |    |
| Fasting blood-glucose                       |                               | X                        |   |    | X  |    |    |
| Immunological analyses                      |                               | X                        |   |    | X  |    |    |
| M. pneumoniae serology               | X                 |                          |   |    | X  |    |    |
| Nasopharyngeal sample for
multivirus PCR | X                 |                          |   |    |    |    |    |
| Upper airway sample             | X                             |                          |   |    | X  |    |    |
| Chest X-ray                                 | X                             |                          |   |    |    |    |    |

 CAP score will be obtained via telephone day 1-6 if the patient has been discharged

 Laboratory parameters will be taken daily until normalised

 *Mycoplasma pneumoniae* serology and upper airway sampling will be taken on day of inclusion

 Upper airway sample for diagnostic *M. pneumoniae* PCR and for subsequent phenotypic and genetic *M. pneumoniae* characterisation

Comorbidities: Will be obtained from the patient and medical records and recorded in clinical records form A. On the day of inclusion a nasopharyngeal aspirate will be taken for analyses of potential co-infection with Influenza A+ B, Parainfluenza 1, 2, 3, Human Bocavirus, Human Metapneumovirus, Coronavirus HKUL, OC43, 229E, NL63, Adenovirus, Enterovirus, Rhinovirus and Respiratory Syncytial virus.

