### **Statistics**

Power calculation: Was done using [www.sealedenvelope.com](http://www.sealedenvelope.com). The significance level was set at 5% and the power at 90%. In the only randomised trial available, cortisone versus not cortisone resulted in defervescence by 48 hours in 100% and 0% respectively and hypoxemia lasted for a mean <2 versus >3 days, respectively. Our power calculation therefore assumes resolution of hypoxemia by 48 hours in 95% of participants with betamethasone and 65% of those without betamethasone. The sample size required in each group would then be 33. Assuming a 5% loss to follow up 70 patients need to be included.

Duration: Approximately one year for patient inclusion and follow up. The trial will end after the last visit of the last subject. A Declaration of End of Trial Notification will be sent to the MPA at the latest 90 days after the study has ended.

Data storage: All CRFs and signed informed consent forms will be collected from all study sites and stored in a locked cupboard in a locked room at Danderyd hospital for at least 10 years. Data will be double entered using EpiData 3.1 by the investigators at Danderyd Hospital. Study ID only will be used on computerised records. The key will be stored with the CRFs at Danderyd Hospital.

Data analysis: The data will be analysed using survival estimates of the primary endpoint. A per protocol and intention to treat analysis will be done. Loss to follow up will be censored at the time of loss to follow up. Final analysis will include a description of included participants, proportions of adverse events and any serious adverse events, the proportion of participants withdrawn or lost to follow up, the cumulative success and failure rates by week 8. Categorical variables will be compared using the  $\chi^2$  test or Fisher exact test and continuous variables using quantile regression.

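### The schedule does not secure a CAP score before randomisation and first betamethasone dose, so the reference point for the secondary endpoint of improvement is undefined

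*Protocol*

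**What the plan says.** - **Endpoint** (Protocol, Outcomes, secondary endpoints): "improvement in subjective well-being, shortness of breath, and cough as determined by CAP score questionnaire". No reference time point for the improvement is named.
- **Timing of the score** (Study Procedures, Monitoring and follow up): "Following inclusion, participants will also be followed up with structured questionnaires (appendix 3, 4 and 5"), to obtain the "CAP) score on days 1, 2, 3, 4, 5, 6, 7, 14, 28, 42 and at 2 months after inclusion". There is no day 0 or baseline entry.
- **Table 1**: the first time-point column covers items collected before or at inclusion. It is marked for form A, CRP/WBC/Hb, serology, virus PCR, upper airway sample and chest X-ray. It is blank for form B/C. That row's footnote ties it to the CAP score: "CAP score will be obtained via telephone day 1-6 if the patient has been discharged".
- **Treatment** (Study Procedures, Treatment): patients allocated to betamethasone "will take 3 mg once daily days 1 and 2". The first dose thus shares its day label with the first CAP score.
- **Blinding** (Study Design): "An open, randomised, controlled, multicentre, clinical trial".
- **Form used at entry** (Study population): "Upon inclusion case record form A will be filled in (appendix 1"). The text links form A to inclusion and comorbidities, not to the CAP score. The appendices are not shown.
- **Analysis** (Statistics, Data analysis): "continuous variables using quantile regression". Covariates are neither listed nor excluded.

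**The concern.** Improvement is a change from some starting value, and the protocol does not fix one. The only candidate is the day-1 score. In an open trial, a patient who answers on day 1 may already know the arm and may already have taken a dose.

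If such a score is used as the starting value, any early drug effect or reaction to the allocation is subtracted from the result. If it is used as a covariate, the analysis conditions on something that treatment may have changed. If it is ignored and later scores are compared directly, the comparison is valid as randomised, but the spread in initial severity stays in the error term of a trial of about 35 patients per arm.

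This is a matter of data collection, so it belongs in the protocol. An analysis plan can choose a model or a definition of change, but it cannot supply a patient-reported baseline that nobody collected.

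**Working it through.** **1. The plan's own figure.** The protocol gives no sample size for the CAP score. Its calculation for the primary endpoint (95% versus 65%, power 90%, significance level 5%, taken as two-sided) reproduces with unpooled variances:

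n per group = (1.960 + 1.282)² × (0.95 × 0.05 + 0.65 × 0.35) / 0.30² = 32.1, rounded up to 33.

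With 5% loss: 66 / 0.95 = 69.5, rounded up to 70. This figure is not in question. It only supplies the 33 evaluable patients per arm used in step 4.

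**2. What day 1 can mean.** Three readings fit the text:

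| Reading of the day-1 score | Knowledge of arm | Drug effect |
|---|---|---|
| After inclusion, before randomisation | no | no |
| After randomisation, before first dose | yes | no |
| After first dose | yes | possible |

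Only the first gives a clean baseline, and nothing in the protocol requires it. Elsewhere the protocol does specify collection before inclusion or on the day of inclusion, for airway samples and serology. With 14 hospitals, practice could differ between sites.

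**3. Effect of using a post-dose day 1 as the starting value (illustration).** Let D be the difference between arms at follow-up and f the share of it already present on day 1 (assumed). The difference in change from day 1 is D − fD = (1 − f)D.

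- f = 0.10: 90% of the effect is recovered
- f = 0.25: 75%
- f = 0.50: 50%

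If the early difference ran the other way (f negative), change would overstate the effect. The documents give no basis for choosing f.

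**4. Precision lost without a clean baseline (illustration).** Let r be the correlation between baseline and follow-up score, assumed 0.3 to 0.7. By the least-squares approximation, adjustment multiplies the standard error by √(1 − r²). The equivalent gain in sample size is 1/(1 − r²).

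With 33 per arm, 90% power and two-sided 5%, the detectable difference on follow-up scores alone is √(2/33) × (1.960 + 1.282) = 0.80 SD.

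| r | SE ratio | SE reduction | Equivalent extra patients | Detectable difference, adjusted |
|---|---|---|---|---|
| 0.3 | 0.954 | 5% | 10% | 0.76 SD |
| 0.5 | 0.866 | 13% | 33% | 0.69 SD |
| 0.7 | 0.714 | 29% | 96% | 0.57 SD |

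Step 4 measures precision only. It does not measure the bias in step 3.

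**The case against.** The best defence is that silence is not exclusion. Several stronger readings are tempting, and the documents do not support them.

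- **That no CAP score precedes randomisation.** A reader might infer this from the schedule. But day 1 is not placed relative to randomisation or first dose, and a score taken after inclusion could still precede both. The contents of form A and of the questionnaires are not visible. The blank cell in Table 1 is also imperfect evidence: the text says pre-inclusion values are entered on form B, yet the table does not mark that form at inclusion. Those values come from medical records, though, and follow a list of physiological measurements, so a questionnaire score would not normally be among them.
- **That improvement cannot be calculated.** It can be calculated from day 1, with a starting value of uncertain status. The arms can also be compared on follow-up scores with no baseline at all, and randomisation protects that comparison.
- **That the quantile regression omits baseline.** The protocol does not say so. Covariates are commonly left to the analysis plan, which is not shown, so this is no fault of the protocol.
- **That first scores will be taken by telephone after discharge.** The footnote is a general provision for days 1 to 6. Patients enter hypoxemic and admitted, and nothing suggests that discharge on day 1 will be usual. The footnote does fit poorly with treating day 1 as a pre-randomisation baseline by design.

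It is also fair to say that the correlations in the working are assumed, that one value is applied to scores from the first week to two months, and that a least-squares formula only approximates quantile regression.

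What remains after all this is the gap itself: the protocol neither fixes when the first score is taken relative to randomisation and first dose nor names the reference for improvement.

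**Conclusion.** The point holds as a gap in the schedule. No CAP score before randomisation and first dose is secured. The reference for improvement is therefore undefined and may be affected by treatment or by knowledge of the arm.

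The size of any resulting bias cannot be derived from the documents. The loss of precision from having no clean baseline is modest to material: a 5 to 29% reduction in standard error forgone, under the assumed correlations and the approximation above. The arms remain comparable on follow-up scores.

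The consequence is limited to the CAP-based secondary endpoints. The primary endpoint and the sample size of 70 are untouched. A reader might infer that a proper baseline would make the CAP results free of open-label bias. It would not, because every later score is still reported by a patient who knows the arm.

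**What to change.** 1. In Table 1, mark the CAP questionnaire in the column for collection before or at inclusion.
2. In Monitoring and follow up, state that it is completed after consent and before randomisation.
3. In Outcomes, name that score as the reference for improvement. In Data analysis, name it as the baseline covariate in the CAP comparisons.

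The cost is one more administration of a short questionnaire already in use, to a patient who is in hospital at the time, plus a few sentences of protocol text. Sample size and follow-up visits do not change.

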### Laboratory Procedures

Analyses of CRP, WBC, Hb, PCRs and serologies will be done at respective hospitals affiliated Laboratory.

Upper airway samples for phenotypic and genotypic characterisation of *M. pneumoniae* will be stored in Universal Transport Medium and frozen at -80C at respective study site. Prior to analysis samples will be collected at irregular intervals and stored centrally at Karolinska Institutet biobank.

Fasting blood glucose values will be analysed on the wards whilst admitted.

Daily whilst admitted and at the day 28 follow up, 15 ml blood samples (10 ml EDTA tube and 5 ml tube without anticoagulants) will be obtained. The EDTA blood will be processed by ficoll centrifugation; obtained PBMC and plasma will be stored at liquid nitrogen and -70C respectively. The serum obtained from 5 ml blood (sampled without anticoagulant) will be stored at -70C.

Soluble factors such as cytokines and chemokines will be evaluated using immunoassays (LUMINEX, ELISA). Flow cytometry will be utilized to evaluate the cellular immune activation (T cells and monocytes). The cellular and soluble immune activation markers will be compared with clinical metadata to reveal the association with disease severity and clinical parameters.

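### The sampling schedule does not require an immunology sample before the first betamethasone dose, which weakens the inflammatory-fingerprint endpoint

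*Protocol*

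**What the plan says.** Three places in the Protocol set the timing of the immunology blood, and they agree.

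- Study Procedures, monitoring and follow up: "Fasting blood glucose and blood samples for immunological analyses will be taken daily until discharge and on day 28".
- Laboratory Procedures: "Daily whilst admitted and at the day 28 follow up, 15 ml blood samples" are to be obtained.
- Table 1: the rows "Immunological analyses" and "Fasting blood-glucose" are marked for each day in hospital and for day 28. Both are blank in the first column, which covers samples before or at inclusion. CRP, WBC and Hb, serology, the multivirus PCR and the upper airway sample are all marked in that column.

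For serology the text also fixes the day: "Blood samples for *M. pneumoniae* serology will be taken on the day of inclusion and at day 28".

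The immunology blood serves the secondary endpoint (Outcomes) of "identifying inflammatory fingerprints for prediction of severe *M. pneumoniae* infection". Laboratory Procedures describes its use: "The cellular and soluble immune activation markers will be compared with clinical metadata to reveal the association with disease severity and clinical parameters". It does not say which sampling day is meant. Under Treatment, betamethasone is given on days 1 to 5 in the randomised arm only. No section relates the clock time of the first dose to any blood draw.

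**The concern.** A marker meant to predict severe infection has to be read before treatment alters it. The planned markers are cytokines, chemokines, T cells and monocytes. The trial's own rationale is that corticosteroid acts on the inflammation behind the illness. A first sample drawn after the first dose therefore mixes disease biology with drug effect, and does so in one arm only.

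The authors did fix inclusion timing for several other tests, but not for the row most directly exposed to the study drug. An analysis plan cannot repair this later, because blood not drawn before the dose cannot be recovered. What is at stake is how usable the treated half of the trial is for the fingerprint endpoint.

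**Working it through.** **1. What the schedule requires.**

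| Place in Protocol | Immunology blood | Tied to first dose? |
|---|---|---|
| Study Procedures, text | daily to discharge, day 28 | no |
| Table 1 | daily in hospital, day 28; inclusion column blank | no |
| Laboratory Procedures | daily in hospital, day 28 | no |

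A pre-dose sample is neither required nor excluded. A draw on the first day could fall on either side of the dose. The day 28 sample comes 28 − 5 = 23 days after the last dose, so it is well clear of dosing, but it is convalescent and cannot predict acute severity.

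**2. How many patients.** Inputs from Power calculation: 95% against 65%, 5% significance (taken as two-sided), 90% power, 5% loss.

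- n per group = (0.95×0.05 + 0.65×0.35) × (1.960 + 1.282)² / 0.30² = 0.275 × 10.507 / 0.09 = 32.1, rounded up to 33. This is the plan's figure.
- With 5% loss: 33 / 0.95 = 34.7, so 35 per group and 70 in total. This is also the plan's figure.
- Allocation is 1:1, so up to 35 of 70 patients could have a post-steroid first sample.

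**3. Pooling the arms and ignoring treatment.** The Protocol gives no marker data, so these are assumptions: a true marker–severity correlation of 0.40, a uniform steroid shift of d standard deviations in the treated arm, and severity itself unchanged by treatment. With half the patients shifted, the marker variance becomes 1 + d²/4, and the pooled correlation is 0.40 / √(1 + d²/4).

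| d (SD) | Formula | Simulation (4000 runs, 35 per arm) |
|---|---|---|
| 0.5 | 0.39 | 0.38 |
| 1.0 | 0.36 | 0.36 |
| 1.5 | 0.32 | 0.32 |

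**4. Adjusting for arm.** With a uniform shift, the within-arm correlation returns to about 0.40 in the same simulations. If the shift varies between patients with standard deviation s, independently of the marker, the treated-arm correlation is 0.40 / √(1 + s²). For s = 0.5 that is 0.40 / 1.118 = 0.36; for s = 1.0 it is 0.40 / 1.414 = 0.28. Without pre-dose samples, the trial cannot check which case applies.

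**5. Using controls only.**

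- Standard errors widen by √(70/35) = 1.41.
- The correlation detectable with 80% power at two-sided 5%, by the Fisher z approximation, is tanh[(1.960 + 0.842)/√(n − 3)]. This gives 0.33 for n = 70 and 0.46 for n = 35.

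**6. Glucose, for comparison.** In standard deviation units, the between-arm difference without a baseline has standard error √(2/35) = 0.24. In simulation with an assumed true effect of 1.0 SD, the mean estimate was 1.00, so it is unbiased. A baseline with correlation ρ multiplies the standard error by √(1 − ρ²). For ρ = 0.3, 0.5 and 0.7 the result is 0.23, 0.21 and 0.17.

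**The case against.** The strongest reply is that the documents leave the timing open and do not exclude a pre-dose draw. Patients are already in hospital at inclusion and are sampled daily, so a first draw before the dose fits the text. The blank cell in Table 1 is weak evidence on its own. The row for clinical records form B/C is also blank in that column, yet the text says form B receives values from before inclusion. Nor does a mark there prove pre-dose timing, since serology is fixed only to the day of inclusion. All of this stands. It limits the point to what the schedule fails to require.

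Four stronger readings might be inferred, and the documents do not support them:

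- **That the immune data are contaminated in half the patients.** This turns a possibility into a certainty.
- **That treated patients have no drug-free value at all.** The day 28 sample is one. What may be missing is a drug-free value from the acute illness.
- **That the hyperglycaemia comparison is spoiled.** The drug's effect on glucose is what the between-arm safety comparison measures. Randomisation protects that comparison without a baseline, diabetes is an exclusion, and the Protocol commits to no change-from-baseline glucose analysis.
- **That the factor of 1.41 is the expected loss.** It applies only if the treated arm is discarded; arm is known and can be adjusted for.

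It can also be said that the choice of sampling day and model terms belongs in an analysis plan, which is not shown. That is fair for the analysis, but not for the draw, which is a collection instruction.

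**Conclusion.** The point holds as a gap in the sampling schedule. The Protocol does not require an immunology sample at inclusion or before the first betamethasone dose, so the first acute-phase sample in up to 35 of 70 patients may be post-steroid. How often this would happen cannot be derived from the documents.

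Under the assumptions stated, ignoring arm lowers a correlation of 0.40 to between 0.38 and 0.32. Adjusting for arm restores it only if the drug shift is uniform. Falling back on controls is the worst case: standard errors 1.41 times wider, and a detectable correlation of 0.46 in place of 0.33.

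The weight is minor to moderate. The fingerprint item is one of several secondary endpoints, and the Protocol describes its analysis as a search for associations. The primary endpoint and the randomised comparisons are unaffected.

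**What to change.** In Table 1, mark the row "Immunological analyses" in the inclusion column with a note that the sample is drawn before the first betamethasone dose. Say the same in the monitoring text of Study Procedures and in Laboratory Procedures. Take the tubes with the serology blood already drawn on the day of inclusion, and use this sample from both arms for the fingerprint analysis. Arm should stay in that analysis, because treatment may still alter the clinical course against which the markers are compared.

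Optionally, draw a glucose at the same time and record fasting status, since that value may not be fasting. It would add precision and within-patient change; it is not needed for an unbiased between-arm comparison.

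The cost is nil in blood if the first daily sample is simply moved ahead of the dose. Otherwise it is one extra 15 ml draw per patient, with PBMC processing at inclusion. No sample size or other stated figure changes.
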